**Methods:**

A prospective, 5-year, open-label, international, multi-centre randomised controlled trial of a minimum of 164 participants with genetically or enzymatically confirmed FD (or both) who have evidence of cardiac disease will be recruited from five centres: Queen Elizabeth Hospital, Birmingham, UK; Salford Royal Hospital, Salford, UK; Royal Free Hospital, London, UK; Addenbrookes Hospital, Cambridge, UK; and Westmead Hospital, Sydney, Australia. Participants will be block-randomised (1:1) to two study arms for cardiac monitoring (i) control arm: standard of care with annual 24 h or 5-day Holter monitor or (ii) treatment arm: continuous cardiac monitoring with ILR implantation plus standard of care. Participants will undergo multiple investigations—blood/urine biomarkers, 12-lead and advanced electrocardiogram (ECG) recording, echocardiography and cardiovascular magnetic resonance (CMR) imaging—at baseline and 6–12 monthly follow-up visits. The primary endpoint is identification of arrhythmia requiring initiation or alteration in therapy. Secondary outcome measures include characterising the risk factors associated with arrhythmia and outcome data in the form of imaging, ECG and blood biomarkers.

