### Assessment and follow-up

Following screening assessment for eligibility, all patients will undergo study entry investigations at their baseline visit. Subsequent follow-up will occur for 3 years at 6–12 monthly intervals, although recruiting centres have the option to review patients more frequently depending on clinical need. All study procedures will be repeated at follow-up visits. Figure 3 summarises the follow-up period and clinical procedures that will be undertaken at each time point. The investigations listed below will be carried out on the whole study population:Blood and urine analysis

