Participants will undergo CMR imaging as part of the research study or as clinically indicated. These will occur at Birmingham (UK), Barts Heart Centre, Manchester Royal Infirmary, Addenbrookes Hospital and Royal North Shore Hospital (Sydney, Australia). A 1.5-Tesla MR system (Avanto (UK), Aera (Australia), Siemens Healthcare, Erlangen, Germany) and a standard protocol including LV cines in short axis (SAX), four-chamber, two-chamber and three-chamber views (ECG R wave gated steady-state free precession imaging) will be used. Native T1-mapping will be performed before and after contrast administration by using a Modified Look-Locker Inversion (MOLLI) recovery sequence (8-mm slice with a 192 read-out matrix, 6/8 phase partial Fourier with 81% phase resolution, repetition time 2.4 ms, echo time 1.01 ms, 11 phases; 3, 3, 5 scheme). The resulting pixel-by-pixel T1 colour map will be displayed by using a customised 12-bit lookup table, where normal myocardium will be defined as purple, increasing T1 as pink/red, and decreasing T1 as dark blue. T2 colour maps will be similarly formed, and increasing T2 will be shown as orange/yellow. LGE imaging will be performed by using phase-sensitive inversion recovery (bolus administration of gadolinium based contrast 0.1 mmol/kg body weight) to quantify the location, pattern and extent of LGE. Image analysis will be performed offline by an accredited cardiologist or radiologist at each centre by using Cvi42 (Circle Cardiovascular Imaging Inc., version 5.3.4, Calgary, AB, Canada) and will include assessment of ventricular mass, volumes, tissue characterisation with T1/T2 mapping and assessment for the presence of LGE by using methodologies previously described [25].4.12-lead ECG and advanced ECG analysis

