#### Planned statistical analysis

Statistical analyses will be carried out by using SPSS 23 (IBM Corporation, Armonk, NY). All continuous variables will be expressed as mean ± standard deviation, and all non-continuous data will be expressed as frequencies or percentages. Normality will be evaluated by using the Shapiro–Wilk test. The independent *t* test will be used to compare parametric data, and the Mann–Whitney *U* test will be used for non-parametric data. Chi-squared or Fisher’s exact tests will be used to compare proportions within two independent groups. For comparisons of repeated sample results, repeated measure analysis of variance (ANOVA) with post-hoc Bonferroni correction will be used. Time-to-event (survival) analysis will be performed to evaluate the presence of arrhythmic events during follow-up. Kaplan–Meier curves will be used to estimate the cumulative probability of arrhythmic events, and Cox proportional hazards regression will be used to evaluate the relationship between predefined covariates and outcome events. A *P* value of less than 0.05 will used for statistical significance.

All patients will have a minimum of 18 months’ follow-up for the primary outcome before interim safety analysis, which will be performed on an intention-to-treat basis. The relationship between arrhythmic burden and all other variables will be analysed by using the methods described above. An alpha spending function method will be used for the interim analysis, and a critical *P* value of less than 0.01 will be used to signify statistical significance.

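### Repeated-measures ANOVA suits the partly optional, centre-dependent visits poorly: it gives up patients or visit records that a linear mixed model would keep (minor; secondary results only)

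*Protocol article*

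**What the plan says.** The Planned statistical analysis section names the software, "Statistical analyses will be carried out by using SPSS 23", and then the method for comparing repeated results: "repeated measure analysis of variance (ANOVA) with post-hoc Bonferroni correction will be used". It does not say which results are meant, and it names no mixed model.

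The data the method would act on are described elsewhere in the article:

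- **Outcomes.** The abstract's Methods paragraph includes among the secondary outcome measures "outcome data in the form of imaging, ECG and blood biomarkers".
- **Schedule.** Under Assessment and follow-up, "Subsequent follow-up will occur for 3 years at 6–12 monthly intervals", and "All study procedures will be repeated at follow-up visits". The same section adds that "recruiting centres have the option to review patients more frequently depending on clinical need".
- **Centre differences.** The Fig. 3 legend describes the shaded visits as optional and dependent on the centre. The Fig. 1 legend gives 12-monthly follow-up for everyone over 36 months, also marked as centre-dependent.
- **CMR.** "Participants will undergo CMR imaging as part of the research study or as clinically indicated".
- **Leaving the study.** Table 2 lists death, withdrawal of consent and adverse events among the reasons. No expected rate is given.

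**The concern.** Classical repeated-measures ANOVA needs the same set of visits for every patient, and the standard SPSS procedure deletes a patient who lacks any one of them. This trial's schedule produces unequal series by design, because some centres hold 6-month visits and others do not. Missed visits, withdrawal and death add to that.

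The analyst would have to choose between two losses. An annual set of visits leaves the extra 6-month records unused. A half-yearly set excludes every patient at an annual-only centre. Either way, a single missed visit removes the patient's whole series. In a rare disease with a planned minimum of 164 participants, that precision is worth keeping. If the patients who leave differ in their earlier values, the completers are also a selected group.

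This concerns a method the article states, not a detail it leaves to the analysis plan.

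**Working it through.** **The plan's own figure.** The only design figure is 80% power for the primary endpoint (5% v 20%, 82 per arm, two-sided alpha 0.05). Exact enumeration of Fisher's test gives 80.5%, so it reproduces. It does not depend on the method for repeated results. The article gives no figure for those results, so the missing rates and covariances below are assumptions.

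**1. Patients kept by a complete-case method.** Let m be the share missing each follow-up visit, independently, and K the number of follow-up visits. The complete share is (1 − m)^K, applied to 164 patients.

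| K | m | Complete share | Patients kept | Patients dropped |
|---|---|---|---|---|
| 3 (annual) | 5% | 0.95³ = 0.857 | 141 | 23 |
| 3 (annual) | 10% | 0.90³ = 0.729 | 120 | 44 |
| 6 (half-yearly) | 5% | 0.95⁶ = 0.735 | 121 | 43 |
| 6 (half-yearly) | 10% | 0.90⁶ = 0.531 | 87 | 77 |

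**2. Cost of each choice of visits, before any missed visit.** Let s be the assumed share of patients at annual-only centres.

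- Half-yearly visits: at most 164 × (1 − s) patients can be complete. That is 131, 98 and 66 for s = 20%, 40% and 60%.
- Annual visits: a half-yearly patient has 7 records, 3 of them unused; an annual-only patient has 4. The unused fraction is 3(1 − s) / [7(1 − s) + 4s], which is 38%, 31% and 23% for the same values of s.

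**3. Precision of the 36-month change.** Assume visits at 0, 12, 24 and 36 months, random intercept SD 0.8, random slope SD 0.15 per year, residual SD 0.45, baseline always observed, and follow-up values missing completely at random.

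- Variance of one patient's change: 3² × 0.15² + 2 × 0.45² = 0.2025 + 0.405 = 0.6075.
- Complete cases: SE = √(0.6075 / patients kept). This is √(0.6075/140.6) = 0.0657 at 5% and √(0.6075/119.6) = 0.0713 at 10%.
- Mixed model with one mean per visit: the information matrix is 164 × Σ P(pattern) × V⁻¹, summed over the eight patterns of observed follow-up visits, where V is the covariance of the observed visits. Inverting it gives SE 0.0618 at 5% and 0.0628 at 10%.
- SE ratio: 1.064 at 5% and 1.135 at 10%.
- Information lost: 1 − 1/1.064² = 0.12 and 1 − 1/1.135² = 0.22.

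These are standard errors for one group of 164. For a difference between arms of 82, both standard errors double and the ratios do not change.

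**4. Cross-check.** A 600-run simulation of the arm difference, with an equal correlation of 0.7 between visits, gave a complete-case variance 1.26 times that of the mixed model at 10% missing (√1.26 = 1.12 in SE) and 1.64 times at 20% (√1.64 = 1.28).

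**5. Bias.** Under one assumed dropout rule that depended on the previous value, the complete-case control-arm change was 0.326 SD against a true 0.300; the mixed model gave 0.300. The rule was the same in both arms, and the arm difference was close to the true −0.300 with either method (−0.303 complete-case, −0.304 mixed model).

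**The case against.** The strongest reply is that little depends on this sentence. All eight items under Secondary outcome measures relate a marker to arrhythmia or its burden, and none is a change in a marker over time. Cox regression is named for relating covariates to events. The link to ANOVA rests on one clause of the abstract and on the statement that procedures are repeated. This stands, and it limits the point to secondary or ancillary longitudinal results.

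Second, a common annual set of visits exists: the Fig. 1 legend gives 12-monthly follow-up for all, and the 12-lead ECG and Holter are annual. This also stands. ANOVA can be run; what it costs is data.

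Third, missing-data handling may be set out in an analysis plan that is not shown. Imputation there could reduce the loss from missed visits. It would be an awkward answer to visits that some centres never schedule.

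A reader might also infer three stronger things that the article does not support:

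- **That CMR is done only on clinical indication.** The text offers research or clinical indication, and Assessment and follow-up applies the investigations to the whole study population.
- **That patients who receive a pacemaker, defibrillator or CRT device drop out.** The ILR removal text keeps them in follow-up.
- **That the longitudinal results will be biased.** The article gives no dropout rate or pattern, and the calculations show mainly a loss of precision. A mixed model would not by itself settle how to treat death or measurements taken after a device is implanted.

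**Conclusion.** The point holds as a minor one. The stated method does not suit the stated schedule, and a better method is available at almost no cost.

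If 5% to 10% of patients miss each of three annual visits, 23 to 44 of 164 are dropped. Under the covariance assumed above, the standard error of the 36-month change is 6.4% to 13.5% larger than with a mixed model, about 12% to 22% of the information. The size depends on those assumptions. A half-yearly set of visits would lose more patients, and the second covariance gave a similar loss at 10% missing.

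Bias would arise if death or withdrawal were related to earlier values. That is plausible, but not shown. The primary endpoint, its power and the listed marker-arrhythmia analyses are not touched.

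**What to change.** Replace the sentence on repeated results with a linear mixed model for repeated continuous measures:

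- use all observed visits, at actual time since randomisation;
- fixed effects for time, arm, arm-by-time and risk group;
- patient random effects;
- baseline entered either as one of the outcomes or as a covariate, not both.

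Repeated-measures ANOVA on the annual visits can stay as a sensitivity analysis. The null hypothesis concerns arrhythmia only, so arm comparisons of markers should be labelled as secondary.

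**Cost.** Only analysis wording changes; SPSS 23 fits these models, and visits and sample size stay as they are. The downside is slightly more modelling work and reliance on data being missing at random. That assumption can fail where death or withdrawal depends on unobserved values, but it is weaker than the one complete-case ANOVA needs.

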### Additional considerations

#### Adverse events and participant withdrawal

All adverse and serious adverse events (SAEs) will be reported in accordance with standard International Council for Harmonisation Good Clinical Practice reporting guidelines. SAEs will be reported within 24 h of identification to the local study investigator and the chair of the clinical events review committee (CERC). All SAEs will be reviewed for causality and ongoing management requirements. Any serious concerns identified by the CERC may result in modification or termination of the study or participant withdrawal. Complete withdrawal criteria are listed in Table 2.

**Table 2 Tab2:** Participant withdrawal criteria

Withdrawal criteria	
Participant’s withdrawal of consent	
An adverse event (AE) or serious adverse event (SAE) requiring withdrawal from study (determined by CERC)	
Death	
Substantial protocol deviation	
Investigator or sponsor decision	

## Discussion

The use of ILRs for arrhythmia detection in general cardiology has increased significantly over the last 10 years. Newer-generation devices are now considerably smaller and require a minimally invasive procedure for implantation, thus carrying much lower peri-procedural risk. The diagnostic yield, in general cardiovascular conditions, from ILR devices is much higher than current standard-of-care ECG monitoring (stand-alone 12-lead ECG or ambulatory Holter ECG monitoring) [32]. However, the benefit of ILR in FD is not defined.

FD is a rare genetic condition characterised by multi-organ involvement, and significant morbidity and mortality occur secondary to cardiovascular involvement. Although SCD remains a significant cause of death, the total incidence of malignant ventricular arrhythmia is variably reported in the literature [33, 34], and there is no clear guidance on treatment. The rarity and complexity of this disease process have led to a paucity of large randomised clinical trials in this area, and no studies to date have been able to fully characterise risk predictors of arrhythmia. One small single-centre study [34] demonstrated the extensive arrhythmic burden in progressive disease; however, this included only patients with advanced Fabry cardiac disease and consequently did not fully characterise arrhythmic risk across the spectrum of Fabry cardiomyopathy.

We have also recently shown that the burden of ventricular arrhythmia is much higher than previously thought. In a multi-centre study of 109 FD patients who had previously undergone cardiac device implantation, the incidence of ventricular arrhythmia requiring medical or device therapy was found to be as high as 25.7% over a 5-year follow-up period [35], thus highlighting the extent of arrhythmic burden. Additionally, suspected arrhythmic risk factors, such as LVH, extensive LGE and prolonged QRS duration, were all found to be highly prevalent in this cohort. Detailed risk stratification and direct correlation with arrhythmia across all FD risk subgroups are crucial in developing a greater understanding of those at risk of life-threatening cardiac arrhythmia.

This study will be the first to identify the true arrhythmic burden in FD and demonstrate the clinical benefit of ILR in arrhythmia detection. Additionally, it will characterise arrhythmic risk across a spectrum of patients with FD by using novel biomarker techniques and will allow direct correlation of atrial and ventricular arrhythmia with underlying structural and functional changes.

## Trial status

This study was due to commence recruitment in January 2019 and have a total recruitment period of 18 months.

## Data Availability

Data obtained from this study will be disseminated and published through international clinical meetings and peer-reviewed journals. Data will also be presented to local sites and regulatory authorities if required.

## Abbreviations

2D: Two-dimensional
AF: Atrial fibrillation
CERC: Clinical events review committee
CMR: Cardiac magnetic resonance
CRT: Cardiac resynchronisation therapy
ECG: Electrocardiogram
FD: Fabry disease
HCM: Hypertrophic cardiomyopathy
hs-CRP: High-sensitivity C-reactive protein
ICD: Implantable cardiac defibrillator
IL-6: Interleukin-6
ILR: Implantable loop recorder
LA: Left atrial
LGE: Late gadolinium enhancement
LV: Left ventricular
LVH: Left ventricular hypertrophy
Lyso-Gb3: Globotriaosylsphingosine
MSSI: Mainz Severity Score Index
MWT: Maximum wall thickness
PPM: Permanent pacemaker
REDCap: Research Electronic Data Capture
SAE: Serious adverse event
SCD: Sudden cardiac death
